### Data Collection and Management

A web-based electronic database (access through the website of the CAPCTG, https://capctg.medbit.cn/) is used for data collection and storage. All data are de-identified and input by the primary investigator or nominated investigators (less than two for each participating center) approved by the primary investigator, and a double check will be done by the research coordinator. Training for data entry is performed by the provider of the electrical database (Unimed Scientific, Inc, Wuxi, China) and the coordinating and data management center of the CAPCTG. Data including demographic characteristics, baseline characteristics, daily laboratory test, daily TG-lowering treatment, daily SOFA score, and follow-up characteristics. Demographic characteristics include age and sex. Baseline characteristics include body mass index (BMI), SOFA score on admission, Acute Physiology and Chronic Health Evaluation II (APACHE II) score on admission, the systemic inflammatory response syndrome (SIRS) on admission. Daily laboratory tests include serum total cholesterol (TC), triglyceride (TG), high-density lipoprotein cholesterol (HDL-c), low-density lipoprotein cholesterol (LDL-c), apolipoprotein A1 (Apo A1), apolipoprotein B (Apo B), apolipoprotein E (Apo E), lipoprotein a [LP(a)], free fatty acids (FFA), C-reactive protein (CRP), and procalcitonin (PCT). Daily TG-lowering treatment includes blood purification treatment (e.g., plasma exchange, hemoperfusion, and hemofiltration) and medical treatment (e.g., insulin and heparin). Follow-up characteristics include ICU days, hospital days, in-hospital cost, revision of the Atlanta classification on admission, CT severity index (CTSI) score (Based on the last image before discharge or death), mortality, and incidence of major complications on day 60. According to the schedule shown in Table 1, the investigators are required to collect data during the index admission and on day 60 after enrollment. And a follow-up on day 60 will be implemented through telephone.

**Table 1 T1:** Schedule of enrollment, assessment and follow up.

	**Study period**			
	**Enrollment**	**Observational period**		**Discharge**
**Time point**	<72 h	Day0^a^	Day1-Day14^b^	Day28 and Day60
**Enrollment:**				
Eligibility screen	X			
Informed consent	X			
Laboratory test	X			
Imaging(CT scan etc.)	X			
**Assessment:**				
Organ failure		X		
Laboratory test		X		
Major treatment		X		
Adverse effects		X		
**Follow up:**				
Vital status				X
Major complication				X
ICU days and hospital days				X
Cost				X

a *Day0 is defined as the day from enrollment to 8 am the next day*.

b *DayX is defined as the day from 8 am day X after enrollment to 8 am the next day*.

: *Assessments during this period need to be repeated on a daily basis*.

### Sample Size Justification

Based on the feasibility and patient flow of the participating sites, a sample size of 300 patients was expected, with an average of 15 patients per month within 2 years. Considering an estimated 20% rate of incomplete data or losses of follow-up, our expected sample size (240 patients) would provide 87% to detect a 2-days (SD: 5) or 82.5% for 1.5-days (SD: 4) improvement of organ failure free days between patients achieve target TG and those not.

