### Study Population

Recruitment started on November 1st, 2020, and is scheduled to end on October 31st, 2022. This study is planned to recruit patients admitted to 30–40 hospitals across China. All adult patients presenting with early HTG-AP with worrisome features would be consecutively enrolled. The definition for HTG-AP with worrisome features is indicated as below.

All adult patients with AP admitted to the participating centers will be assessed for eligibility after admission (Figure 1). The inclusion and exclusion criteria are as follows:

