### Statistical Analysis

Continuous normally distributed data were reported as means with SDs. Skewed continuous data were reported as medians and interquartile ranges (IQRs). Categorical data will be summarized by counts and percentages. The intergroup difference will be compared by Student's *t*-test or Wilcoxon rank-sum test for continuous variable depending on their normality and chi-square test for categorical data.

To evaluate the association between TG decline and OF free days, the study patients will be dichotomized depending on whether the TG level reaches 5.65 mmol/L on Day 3 (the day of enrollment is labeled Day 1, the next day labeled Day 2, and the following day Day 3). For the primary outcome comparison, Wilcoxon rank-sum test will be employed. However, since OF could be evaluated with a time-to-event analysis censored at 14 days to account for the mortality as a competing event, Fine and Gray competing risk regression is used to assess the group difference as a supportive analysis.

For the association between different TG lowering therapy and OF free days, we considered the possibility that baseline characteristics, which were expected to be prognostic for OF, differ according to the choice of TG lowering therapies (i.e., blood purification treatment and medical treatment). A propensity score matching will be further used to compensate for the intergroup unbalance.

For secondary outcomes, a multivariate analysis generalized linear model (GLM) model will be performed to identify its association with TG decline and TG-lowering therapy with proper link and distribution function. The variable included in the model will be age, sex, TG level at enrollment, and other baseline variables that have significant differences between groups.

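### The stated 87% and 82.5% power are equal-group t-test figures, but an observed Day 3 TG value sets the groups and the test is Wilcoxon; separately, 15 patients a month for 24 months is 360, not 300

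*Protocol article*

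**What the plan says.** All references are to the Protocol article.

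- **Sample Size Justification, accrual:** "a sample size of 300 patients was expected, with an average of 15 patients per month within 2 years". A 20% allowance for incomplete data or loss to follow-up then reduces 300 to 240.
- **Sample Size Justification, power:** "our expected sample size (240 patients) would provide 87% to detect a 2-days (SD: 5) or 82.5% for 1.5-days (SD: 4) improvement". The contrast is "improvement of organ failure free days between patients achieve target TG and those not". The section states no significance level, no test and no expected share of patients reaching target.
- **Study Population:** "Recruitment started on November 1st, 2020, and is scheduled to end on October 31st, 2022", a window of 24 months.
- **Statistical Analysis:** "the study patients will be dichotomized depending on whether the TG level reaches 5.65 mmol/L on Day 3", and "For the primary outcome comparison, Wilcoxon rank-sum test will be employed".
- **Primary Outcome Measure:** the outcome is counted to 14 days, and patients with organ failure at day 14 or who died before then are given zero.
- **Exclusion Criteria (closing text):** there is no randomization, and treatment is left to the treating physicians.

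**The concern.** The two powers are printed without conditions, to the nearest percent or half percent. A power for comparing two means depends on how the total is divided between the groups. Here the division is not a design choice: it is whatever share of patients has reached the TG threshold on Day 3. If the printed values assume equal groups, they show the study at its most favourable split for a t-test. A null result from uneven groups would then be read as better powered than it was.

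The test behind the power also appears to differ from the planned one. And the accrual sentence gives a rate, a duration and a total that do not multiply out, although feasibility is the only stated basis for the sample size.

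**Working it through.** **Inputs.** From Sample Size Justification: 300 enrolled, 20% lost, 240 evaluable; differences of 2 days (SD 5) and 1.5 days (SD 4). Assumed, because not stated: two-sided 5% significance level, and the split.

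**Step 1: reproduce the stated power.** Standardized differences are 2/5 = 0.400 and 1.5/4 = 0.375. For a two-sample t-test the noncentrality is d × √(n₁n₂/N), with N − 2 = 238 degrees of freedom. At 120 and 120, √(120 × 120/240) = √60 = 7.746.

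- 2 days, SD 5: 0.400 × 7.746 = 3.098, power 86.99% (stated 87%).
- 1.5 days, SD 4: 0.375 × 7.746 = 2.905, power 82.46% (stated 82.5%).

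Both match as printed. By normal approximation, a one-sided 5% level gives 92.7% and 89.6%, and 150 per group gives 93.4% and 90.1%; neither matches. The printed powers are therefore those of a two-sided 5% t-test with equal groups of 120.

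**Step 2: vary the split.** With N fixed at 240, n₁n₂ is largest when n₁ = n₂, so the t-test values in Step 1 are a maximum.

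| Split | n₁/n₂ | √(n₁n₂/N) | 2 days, SD 5 | 1.5 days, SD 4 |
|---|---|---|---|---|
| 50:50 | 120/120 | 7.746 | 87.0% | 82.5% |
| 60:40 | 144/96 | 7.589 | 85.6% | 80.9% |
| 65:35 | 156/84 | 7.389 | 83.7% | 78.8% |
| 70:30 | 168/72 | 7.099 | 80.7% | 75.5% |
| 75:25 | 180/60 | 6.708 | 76.2% | 70.7% |
| 80:20 | 192/48 | 6.197 | 69.5% | 63.9% |

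T-test power falls below 80% when the smaller group is about 29% of patients in the first scenario (69 of 240) and about 37.5% in the second (90 of 240).

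**Step 3: the planned test.** On normal data with 120 per group, simulated Wilcoxon power is 85.6% and 80.6%, less than 2 points below the printed values. But the outcome is bounded between 0 and 14 with zeros assigned, so the normal case does not describe it. Two illustrative simulations, with assumed clusters at 0 and 14, the rest spread evenly over days 1 to 13, and 120 per group, go in opposite directions:

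- Zeros fall from 25% to 15% and full scores rise from 35% to 53.2% (means 7.70 and 9.67): Wilcoxon about 82%, t-test about 76%.
- Zeros fall from 25% to 10.7% with full scores unchanged at 35% (means 7.70 and 8.70): Wilcoxon about 25%, t-test about 28%.

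The second pair is low because the assumed difference is only 1 day. What matters is the order of the two tests, which depends on where the effect falls. The documents do not say where that is.

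**Step 4: accrual.** 15 × 24 = 360, not 300. Enrolling 300 takes 300/24 = 12.5 per month, or 300/15 = 20 months at 15 per month. The loss allowance does not explain the gap, because it is applied afterwards: 300 × 0.8 = 240. If 15 per month is the intended figure, 360 × 0.8 = 288 evaluable, and t-test power at 144 per group is 92.3% and 88.7%.

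**The case against.** The strongest reply is that the arithmetic is right for what it assumes, and the documents give no expected share reaching target. A near-equal split is as consistent with them as 80:20. At 60:40 the loss is under 2 points in either scenario. A reader might infer that the design will not deliver the stated power, or that the figures fail at anything but exactly equal groups. Neither is supported: the split is unknown, and moderate imbalance costs little.

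A reader might also infer that choosing Wilcoxon lowers the power. That is not supported either. The usual small loss relative to a t-test applies to normally shaped data, and on a bounded outcome with assigned zeros the direction can go either way. For the same reason, 87% and 82.5% are a ceiling for the t-test only, not for the planned test.

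A third tempting reading is that the accrual slip corrupts the power. It does not. The article uses 300 and then 240 consistently, and the monthly rate enters no power calculation. If 15 per month were right, the study would have more power, not less.

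Finally, it may be said that power is a side remark in an observational cohort sized on feasibility, and that a condensed article may leave the split, test and significance level to the full protocol. The sizing point is fair and limits the consequence. But the article prints specific powers, and its own Statistical Analysis section sets a grouping rule and a test that do not match the calculation behind them. What stands is a best case stated without its condition, plus a product that is wrong on the page.

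**Conclusion.** The point holds in a limited form. The printed powers are equal-group t-test figures, given without that condition, for a comparison whose group sizes are observed and whose test is Wilcoxon. For a t-test at 240 patients they are the maximum. The shortfall is under 2 points at 60:40, about 6 to 7 points at 70:30, and about 17 to 19 points at 80:20. These sizes rest on the stated differences and SDs, a two-sided 5% level, and splits that are assumptions here. The effect of using Wilcoxon cannot be signed from the documents, so the split is the main demonstrable source of lost power.

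The accrual sentence is wrong as written, by 60 patients (360 against 300), and stands apart from the power calculation.

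**What to change.** Rewrite the Sample Size Justification paragraph as follows.

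- State the test, significance level and split behind 87% and 82.5%, and label them as equal-group t-test values.
- Give power as a range over splits from 50:50 to 80:20. For the planned Wilcoxon test, obtain it by simulation under a stated distribution of organ-failure-free days, including the share of assigned zeros.
- Correct the accrual sentence: either 12.5 per month for 300 patients over 24 months, or 360 expected with 288 evaluable and the power recomputed from 288.

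The cost is one paragraph and a short simulation. No extra patients are needed. The downside for the sponsor is a stated power that looks less favourable.

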### Statistical Analysis

Continuous normally distributed data were reported as means with SDs. Skewed continuous data were reported as medians and interquartile ranges (IQRs). Categorical data will be summarized by counts and percentages. The intergroup difference will be compared by Student's *t*-test or Wilcoxon rank-sum test for continuous variable depending on their normality and chi-square test for categorical data.

To evaluate the association between TG decline and OF free days, the study patients will be dichotomized depending on whether the TG level reaches 5.65 mmol/L on Day 3 (the day of enrollment is labeled Day 1, the next day labeled Day 2, and the following day Day 3). For the primary outcome comparison, Wilcoxon rank-sum test will be employed. However, since OF could be evaluated with a time-to-event analysis censored at 14 days to account for the mortality as a competing event, Fine and Gray competing risk regression is used to assess the group difference as a supportive analysis.

For the association between different TG lowering therapy and OF free days, we considered the possibility that baseline characteristics, which were expected to be prognostic for OF, differ according to the choice of TG lowering therapies (i.e., blood purification treatment and medical treatment). A propensity score matching will be further used to compensate for the intergroup unbalance.

For secondary outcomes, a multivariate analysis generalized linear model (GLM) model will be performed to identify its association with TG decline and TG-lowering therapy with proper link and distribution function. The variable included in the model will be age, sex, TG level at enrollment, and other baseline variables that have significant differences between groups.

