## Abstract

**Background:** Acute pancreatitis (AP) is a potentially life-threatening inflammatory disease with multiple etiologies. The prevalence of hypertriglyceridemia-induced acute pancreatitis (HTG-AP) has been increasing in recent years. It is reported that early triglyceride (TG) levels were associated with the severity of the disease, and TG- lowering therapies, including medical treatment and blood purification, may impact the clinical outcomes. However, there is no consensus regarding the optimal TG-lowering therapy, and clinical practice varies greatly among different centers. Our objective is to evaluate the TG-lowering effects of different therapies and their impact on clinical outcomes in HTG-AP patients with worrisome features.

**Methods:** This is a multicenter, observational, prospective cohort study. A total of approximately 300 patients with HTG-AP with worrisome features are planned to be enrolled. The primary objective of the study is to evaluate the relationship between TG decline and the evolution of organ failure, and patients will be dichotomized depending on the rate of TG decline. The primary outcome is organ failure (OF) free days to 14 days after enrollment. Secondary outcomes include new-onset organ failure, new-onset multiple-organ failure (MOF), new-onset persistent organ failure (POF), new receipt of organ support, requirement of ICU admission, ICU free days to day 14, hospital free days to day 14, 60-day mortality, AP severity grade (Based on the Revised Atlanta Classification), and incidence of systemic and local complications. Generalized linear model (GLM), Fine and Gray competing risk regression, and propensity score matching will be used for statistical analysis.

**Discussion:** Results of this study will reveal the current practice of TG-lowering therapy in HTG-AP and provide necessary data for future trials.

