## Background

Acute pancreatitis (AP) is a potentially life-threatening inflammatory disease caused by multiple etiologies, such as alcohol, gallstones, and hypertriglyceridemia (HTG). HTG is the third most common cause of AP, accounting for 4–10% of cases globally, and the increasing prevalence of HTG-AP had been reported in recent studies (1–4). In China, HTG had been the second leading cause of AP, and previous studies showed that HTG-AP patients had a higher risk of severe acute pancreatitis and multiple organ dysfunction syndrome (MODS) than other types of AP (2, 5–7).

Although the pathophysiology underlying HTG-AP remains controversial, it is widely accepted that free fatty acid (FFA) is one of the driving factors (8). FFA, produced by the hydrolysis of triglyceride (TG), can initiate or worsen the disease by triggering inflammatory reactions, damaging the pancreatic cell, and promoting microvascular thrombosis within the pancreatic tissue (9). Nawaz et al. (6) found that elevated serum TG levels in AP patients were independently and proportionally correlated with persistent organ failure (POF) regardless of etiology. In an observational study conducted by Lu et al. (10) timely reduction of serum TG during the early phase of HTG-AP was found to be associated with decreased incidence of POF.

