### Exclusion Criteria

Failure to Obtain Informed Consent;Pregnant or Lactating Women; Or Have a Pregnancy Plan Within a Month After the Study (Including Male Subjects);Researchers' Family Members who Are Directly Involved in the Study;Patients Are Expected to die Within 48 H After Enrollment, Defined as Patients With Norepinephrine Usage at a Dose of 25 mg/min or More Under Full-Fluid Resuscitation, With a Systolic Blood Pressure <90 mm Hg and Serum pH Values <7.0. The Judgment Will be Made by the Treating Physician.

Informed consent should be sought for each participant or a patient's relative. They are free to withdraw from the study for any reason without the need for further explanation. This prospective observational study examines clinical outcomes in early HTG-AP patients with worrisome features treated with TG lowering therapy (from fasting to sophisticated blood purification). Therefore, no mandatory intervention or randomization is proposed. The main treatment modalities for TG-lowering therapy include fasting, medical treatment (either heparin, insulin, or both), and blood purification, including hemoperfusion, hemofiltration, and therapeutic plasmapheresis. The treatment is at the discretion of treating physicians.

We recommend all patients receive standard treatment that follows the “Acute Pancreatitis Treatment Guidelines” issued by the American College of Gastroenterology (ACG) in 2013 and the standard treatment plan for acute pancreatitis provided in the “Evidence-Based Guidelines for the Treatment of Acute Pancreatitis” issued by the International Association of Pancreatology (IAP) and the American Pancreatic Association (APA) (23, 24).

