### Primary Outcome Measure

The primary outcome is organ failure (OF) free days to 14 days after enrollment. Only the final period of OF-free days is included, and patients who have OF at day 14 or died before day 14 are assigned to zero OF-free days.

Secondary outcome measures

Part I: Secondary outcomes during the index admission

New-onset organ failure;New-onset multiple-organ failure (MOF);New-onset persistent organ failure (POF);New receipt of organ support;Requirement of ICU admission;ICU free days to day 14;Hospital free days to day 14;

Part II: Secondary outcomes within 60 days after enrollment

Mortality censored at 60 days after enrollment;AP severity grade (Based on the Revised Atlanta Classification);Incidence of infected pancreatic necrosis (IPN);Incidence of septic shock;Incidence of abdominal bleeding;Incidence of gastrointestinal fistula.

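### The primary comparison of a non-randomised exposure is an unadjusted Wilcoxon test, which leaves it open to confounding by enrolment TG and baseline severity

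*Protocol article*

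**What the plan says.** All references are to the Protocol article.

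- **Design.** The text under Exclusion Criteria says "Therefore, no mandatory intervention or randomization is proposed" and "The treatment is at the discretion of treating physicians".
- **Exposure.** Statistical Analysis states that "the study patients will be dichotomized depending on whether the TG level reaches 5.65 mmol/L on Day 3". The Abstract words it differently: "patients will be dichotomized depending on the rate of TG decline".
- **Outcome.** Primary Outcome Measure: "The primary outcome is organ failure (OF) free days to 14 days after enrollment". Only the final failure-free period counts. Patients with organ failure at day 14, or who die before it, score zero.
- **Primary test.** Statistical Analysis: "For the primary outcome comparison, Wilcoxon rank-sum test will be employed". A Fine and Gray regression is added as a supportive look at the group difference, with no covariates named.
- **Adjustment elsewhere in the same section.** Propensity score matching is planned for therapy choice (blood purification or medical treatment) and organ-failure-free days. A GLM relates secondary outcomes to TG decline and to therapy; of its covariates the section says "The variable included in the model will be age, sex, TG level at enrollment", plus baseline variables that differ significantly between groups.
- **Prognostic role of TG.** The Background reports that "elevated serum TG levels in AP patients were independently and proportionally correlated with persistent organ failure".

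**The concern.** Whether a patient reaches 5.65 mmol/L by Day 3 is not assigned. It follows from the starting TG, the treatment the physician chose and the course of the illness. Inclusion Criteria set a floor for enrolment TG but no ceiling, and they admit patients with or without organ failure. The two groups may therefore differ at baseline in factors that bear on organ-failure-free days.

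The plan sees this risk in two neighbouring places. It matches on a propensity score for the therapy contrast, and it adjusts the secondary outcomes for enrolment TG. Study Objectives call the secondary endpoints hypothesis generating. The exploratory results for TG decline are thus adjusted, while the primary result for the same exposure is not, and no reason is given.

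At stake is the interpretation of the main result. A difference between the groups could reflect a real relation with TG decline, baseline differences, or both, and the stated test cannot separate them. Confounding could also hide a real relation.

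**Working it through.** **1. The plan's own power figures.** Inputs from Sample Size Justification: 300 × (1 − 0.20) = 240 analysable patients; differences of 2 days (SD 5) and 1.5 days (SD 4). Significance level and group split are not stated; two-sided 5% and 120 per group are assumed. A two-sample t-test then gives 87.0% and 82.5%, matching the stated 87% and 82.5%. The stated power therefore corresponds to an unadjusted comparison of two equal groups.

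**2. Dependence of the exposure on enrolment TG.** Fall needed = 1 − 5.65 / enrolment TG.

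| Enrolment TG (mmol/L) | Fall needed |
|---|---|
| 11.3 (entry limit) | 1 − 5.65/11.3 = 50% |
| 22.6 | 1 − 5.65/22.6 = 75% |
| 56.5 | 1 − 5.65/56.5 = 90% |

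A fixed level is harder to reach from a higher start. With the cited relation between TG and persistent organ failure, enrolment TG meets both conditions for a confounder on the article's own text.

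**3. Effect of a baseline shift on the crude test.** Suppose reaching the target has no effect, but baseline differences shift the group means by b days. With 120 per group, SE = SD × √(2/120), which is 0.645 (SD 5) or 0.516 (SD 4). The chance of p < 0.05 is 1 − Φ(1.96 − b/SE) + Φ(−1.96 − b/SE). For b = 1 and SD 5, b/SE = 1.549 and the result is 34%.

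| b (days) | SD 5 | SD 4 |
|---|---|---|
| 0 | 5% | 5% |
| 0.5 | 12% | 16% |
| 1.0 | 34% | 49% |
| 1.5 | 64% | 83% |

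The values of b are assumptions.

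**4. Simulation with a generic confounder, no true effect.** N = 240, outcome rounded and bounded at 0–14 days, one measured confounder, 1,000 replicates per setting. Assumed correlations: 0.2–0.5 with the latent exposure and 0.2–0.4 with the outcome. The Wilcoxon test rejected in 7% to 69% of replicates, with spurious differences of 0.25 to 1.28 days. A rank regression adjusted for the confounder rejected in 4% to 6%, and the adjusted mean difference was about 0 days.

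**5. Simulation with enrolment TG as the confounder, no true effect.** Assumed: enrolment TG = 11.3 × exp(exponential variable, mean 0.6); a median of 30% of TG remaining at Day 3 (log SD 0.5), so about half the patients reach the target; organ failure in 45% at mean log TG, with exponential duration.

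- At organ-failure odds ratios of 1.0, 1.4, 1.6 and 2.0 per doubling of enrolment TG, the Wilcoxon test rejected in about 5%, 19%, 31% and 55%. Spurious differences were about 0, 0.4, 0.6 and 0.8 days. Adjusting for log enrolment TG gave 5% to 7%.
- Other outcome models with the same TG assumptions gave as little as 14%, 23% and 41% at odds ratios of about 1.4, 1.6 and 2.0.
- A narrower TG spread (mean 0.3, 40% remaining) gave only 8% to 10%.
- Now add severity: 40% organ failure, odds ratio 1.6 per doubling of TG and 2 per SD of severity. If sicker patients are treated harder, so that log TG falls 0.25 more per SD of severity, the crude test's rejection rate drops from about 30% to about 4%. The two biases then nearly cancel. With the opposite sign they would add.

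**6. Cost of adjustment.** With r_x and r_y the correlations of the confounder with latent exposure and outcome, adjusted SE = SD × √(1 − r_y²) × √(2/120) / √(1 − 2r_x²/π). Over the range in step 4, power is 83–92% for 2 days (SD 5) and 78–88% for 1.5 days (SD 4), against 87% and 82.5% as stated.

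**The case against.** **Direction and size are not established.** A reader might infer that the result is confounded in favour of patients who reach the target, and that severity adds to this. The article does not support that. Physicians choose the treatment, plasmapheresis is described as among the most efficient ways to lower TG, and the plan itself expects prognostic factors to differ by therapy. If sicker patients get more intensive lowering, severity pulls the other way, as step 5 shows. This objection stands. It does not rescue the crude test, because two biases that may or may not cancel are no basis for a primary analysis.

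**The simulated rates are not estimates.** The TG distribution, odds ratios and outcome model are not in the article, and the rates move widely with them. The shifts in step 5 are also smaller than the 1.5 to 2 days the study is powered for. This stands too: the figures illustrate the mechanism only.

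**Adjustment is not confined to secondary outcomes.** Propensity score matching covers organ-failure-free days for the therapy contrast, and a Fine and Gray model can carry covariates. Both are true. But the matching addresses a different exposure, and the regression is supportive with no covariates named.

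**The objective speaks of a relationship.** A crude comparison does describe an association, so it would be too strong to say that the objective cannot be answered at all. The Sample Size Justification, however, speaks of an improvement, and the Discussion motivates the study by bias in retrospective work. Prospective collection alone does not remove baseline confounding.

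**Detail may sit in an unseen analysis plan.** That would excuse a missing covariate list. Here the article names the primary test, and that test takes no covariates.

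**Conclusion.** The point holds as a risk, not as a demonstrated bias. The stated primary test for a non-randomised exposure is unadjusted, although the plan adjusts the same exposure for secondary outcomes. Enrolment TG bears on attaining a fixed level by arithmetic and on organ failure by the article's own citation. Baseline organ failure bears directly on the outcome. The primary result is therefore open to confounding by both.

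The direction and size are unknown. Under assumptions not taken from the article, the crude test's null rejection rate runs from near 5% to above 40%. Adjustment for a measured confounder brings it back to about 5% when that confounder is the only one. Adjusting for enrolment TG alone would leave any bias through severity, so both belong in the model. The stated power is not in error; it describes the unadjusted comparison.

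**What to change.** Change the primary analysis in Statistical Analysis to a prespecified covariate-adjusted model of organ-failure-free days on target attainment, for example proportional-odds regression.

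- Fix the covariates in advance, not by significant baseline differences: at least log enrolment TG, baseline SOFA or organ failure (or APACHE II), age and sex.
- Report the adjusted effect with its 95% CI.
- Keep the Wilcoxon test as the unadjusted description.
- State that residual confounding remains and limits causal reading.
- Optionally, add a sensitivity analysis with log(Day-3 TG / enrolment TG) as a continuous exposure, because the Abstract describes the exposure as a rate of decline.

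The cost is wording. Enrolment TG is needed for eligibility, and Data Collection and Management lists age, sex, SOFA and APACHE II. The downsides are a model assumption to check and possibly a slightly wider interval; step 6 suggests that little or no power is lost.
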